## Abstract

Perfectionism is characterized by setting high standards and striving for achievement, sometimes at the expense of social relationships and wellbeing. Despite sometimes being viewed as a positive feature by others, people with perfectionism tend to be overly concerned about their performance and how they are being perceived by people around them. This tends to create inflexible standards, cognitive biases, and performance-related behaviors that maintain a belief that self-worth is linked to accomplishments. Cognitive behavior therapy has been shown to be a viable treatment for perfectionism, both in terms of reducing levels of perfectionism and improving psychiatric symptoms. Furthermore, a number of recent studies indicate that it can be successfully delivered via the Internet, both with regular support and guidance on demand from a therapist. In the present study protocol, a clinical trial for perfectionism is described and outlined. In total, 128 participants will be recruited and randomized to either a treatment that has already been demonstrated to have many benefits, Internet-based Cognitive Behavior Therapy for perfectionism (iCBT-P), or an active comparison condition, Internet-based Unified Protocol (iUP), targeting the emotions underlying depression and anxiety disorders. The results will be investigated with regard to self-reported outcomes of perfectionism, psychiatric symptoms, self-compassion, and quality of life, at post-treatment and at six- and 12-month follow-up. Both iCBT-P and iUP are expected to have a positive impact, but the difference between the two conditions in terms of their specific effects and adherence are currently unknown and will be explored. The clinical trial is believed to lead to a better understanding of how perfectionism can be treated and the specificity of different treatments.

## Introduction

1

Perfectionism refers to the disposition to set high standards and strive for achievement, typically characterized by the refusal to accept actions and results that fall short of perfection. According to Shafran, Cooper, and Fairburn (2002, p. 778), perfectionism is characterized by *“the overdependence of self-evaluation on the determined pursuit of personally demanding, self-imposed standards in at least one highly salient domain, despite adverse consequences”*. As such, people with perfectionism tend to link their sense of self-worth to the realization of subjectively imposed far-reaching goals, making them prone to self-criticism and negative self-evaluation when these are not met. It is believed that at the core of perfectionism lies highly rigid demands that set the occasion for inflexible rules and intermediate beliefs, e.g., “I cannot make mistakes” and “If I do not succeed at this, I am utterly useless”. This will in turn generate various cognitive biases and performance-related behaviors that maintain the need for perfection, for example, dichotomous thinking (i.e., seeing outcomes as either black or white), selective attention (disregarding the positives), and repeated checking and seeking reassurance from others (Shafran et al., 2016).

Because perfectionism is considered to have trait-like features it is not regarded as a condition with clear boundaries between functional and dysfunctional distributions. Hence, cutoffs differentiating normal and pathological perfectionism are difficult to establish, which makes it hard to estimate the prevalence rate of those in need of treatment. However, empirical evidence demonstrates that perfectionism can lead to a number of detrimental consequences and is elevated among patients with psychiatric disorders (Egan et al., 2011). Perfectionism is for instance associated with a persistent fear of failure and negative evaluation and various emotional, social, physical, cognitive, and behavioral implications (Stoeber, 2017). A systematic review and meta-analysis by Limburg et al. (2017) of 284 studies also examined the relationship between perfectionism and psychopathology. In line with the present understanding of perfectionism, the findings separate the two higher-order dimensions that constitute the construct. First, *perfectionistic strivings*, the propensity to set high standards and being demanding of yourself. Second, *perfectionistic concerns*, the inclination of being self-critical in terms of your own actions, being preoccupied by how others perceive yourself, and having difficulties feeling content about your performance (Stoeber et al., 2020). Although both dimensions are correlated with psychiatric symptoms, perfectionistic strivings seem to be primarily linked to eating disorders (*r* = .36 for bulimia nervosa and .56 for anorexia nervosa). Meanwhile, perfectionistic concerns were mainly related to general psychological distress (*r* = .42), depression (*r* = .40), and anxiety disorders (*r* = .30), potentially revealing distinctive clinical profiles (Limburg et al., 2017). In a recent study of possible mediators, Smith et al. (2020) revealed two reasons for this negative impact. One being due to increased stress, as perfectionistic individuals engage in more stressful activities overall and interpret minor setbacks as failures. The second being cause by so-called social disconnection, that is, the tendency to interpret social interactions as being characterized by criticism, which can lead to isolation and focus on achievement at the expense of closer social relationships (Chen et al., 2015).

### Treating perfectionism

1.1

Perfectionism is regarded as a transdiagnostic phenomenon that can be problematic in itself, but that is also involved in processes that can create or maintain other psychiatric symptoms. This notion is confirmed by the fact that perfectionism is elevated in many conditions, that it predicts the onset and recovery from depression, and that it has strong links to, for example, obsessive-compulsive disorder and social anxiety disorder (Egan et al., 2011). Perfectionism can also affect the course of treatment for these conditions by leading to poorer therapeutic alliance, non-response, and drop-out, particularly with regard to the engagement with certain interventions, such as exposure to fearful stimuli or using behavioral activation (Egan et al., 2016). Hence, there are several reasons to be aware of perfectionism among patients as it can affect both adherence to treatment and result in worse prognostic outlook and increase the risk of relapse. For this reason, Shafran et al. (2002) proposed a cognitive-behavioral conceptualization of perfectionism that can help guide therapists in their assessment and treatment. This stems from their definition of perfectionism being characterized by tightly held inflexible standards, and intends to target cognitive biases and performance-related behaviors, such as via behavioral experiments. Four components were considered important: 1) providing psychoeducation about perfectionism and creating an individualized conceptualization 2) broadening the domains for self-evaluation 3) testing out beliefs and predictions, and 4) addressing personal standards and self-criticism. The treatment has been developed into a manual (Egan et al., 2016), and a self-help book (Shafran et al., 2018), which can be used either stand-alone or in relation to other evidence-based interventions when perfectionism is relevant to address.

To date, the above-mentioned treatment has been evaluated in a series of clinical trials and different settings and formats, such as one-on-one face-to-face, in groups, and unguided self-help. A systematic review and meta-analysis of cognitive behavior therapy involving eight studies demonstrated moderate to large within-group effect sizes Hedge's *g* of 0.79, 95% Confidence Interval (CI) [0.44, 1.14] and 1.33, 95% CI [1.02, 1.64] for self-reported outcomes of perfectionism, while simultaneously having a moderate positive impact on anxiety (.52), 95% CI [0.23, 0.81], and depression (.64), 95% CI [0.35, 0.92] (Lloyd et al., 2015). Recently, several examples of administering the treatment via the Internet have also been evaluated with promising results. In these studies, the outline has been mirrored but delivered as guided self-help programs of 8–12 weeks, demonstrating intention-to-treat between-group effect sizes of Cohen's *d* of 1.01, 95% CI [0.63, 1.39] for perfectionistic concerns, and .67, 95% CI [0.31, 1.04] for perfectionistic strivings (Shafran et al., 2017), and 1.00, 95% CI [0.66, 1.33], and .68 [0.36, 1.00], respectively in Rozental et al. (2017), with maintained benefits at both six and 12 months (Rozental et al., 2018). One study also examined the use of guidance-on-demand with similar results, 1.00, 95% CI [0.51, 1.47], and .72, 95% CI [0.24, 1.18] (Zetterberg et al., 2019). In another systematic review and meta-analysis consisting of 10 studies it was also observed that such a format is comparable to seeing a therapist individually face-to-face (Suh et al., 2019). Thus, it can be suggested that cognitive behavior therapy delivered via the Internet can be helpful in overcoming perfectionism and related psychiatric symptoms. Internet-based treatments are generally seen as a viable option for various conditions, e.g., depression, anxiety disorders, and psychosomatic issues, with similar outcomes as other means of delivery, with the advantage of being available regardless of geographical location (Andersson, 2018). Given that perfectionism might not always be recognized as something that warrants clinical attention in routine care, and due to the lack of trained therapists, Internet-based cognitive behavior therapy could help disseminate an effective treatment for this type of problem (Andersson et al., 2019).

### Study protocol for a randomized controlled trial

1.2

So far, cognitive behavior therapy has been shown to produce outcomes whereby perfectionistic individuals are able to manage the difficulties associated with having to unremittingly strive for achievement and attaining certain standards. This has been confirmed not only by reduced levels of self-reported perfectionism (Lloyd et al., 2015; Suh et al., 2019), but also qualitative investigations demonstrating that patients learn how to deal with situations differently, become better at shifting focus from performance, and broaden the domains for self-evaluation (Rozental et al., 2020). In addition, preliminary evidence implies that psychiatric symptoms can be targeted using cognitive behavior therapy for perfectionism despite not being specifically addressed (Kothari et al., 2019). However, additional studies are needed in order to replicate the results. In particular, comparing two forms of treatment is important to get a better idea of the true effects given that an inactive comparator, e.g., waiting list, can yield inflated results (Cuijpers and Cristea, 2016). In Suh et al. (2019), only half of the 10 clinical trials included in their systematic review and meta-analysis included some form of treatment, which mostly consisted of providing participants with a self-help book. Hence, in the present study protocol, the comparison between two forms of cognitive behavior therapy will be described and outlined; the manual developed by Egan et al. (2016), here referred to as Internet-based Cognitive Behavior Therapy for Perfectionism (iCBT-P), which has been tested on several occasions, and Internet-based Unified Protocol (iUP), a transdiagnostic manual that intends to target the emotional aspects underlying the symptoms involved in depression and anxiety disorders (Ellard et al., 2010). Studies this approach have demonstrated promising results when examined in itself and when compared to treatments that are diagnosis-specific (Barlow et al., 2017; Bullis et al., 2014; Farchione et al., 2012). As to date, Unified Protocol has not been tested for perfectionism, but given its focus on the emotions involved in many conditions, it is reasonable to think that it will have a positive impact on the emotional responses that accompany perfectionism. Moreover, given that iCBT-P and iUP were originally developed for different purposes, that is, perfectionism versus psychiatric symptoms, a clinical trial makes it possible to explore the specificity of the two treatments.

The clinical trial will thus test two treatments for perfectionism over eight weeks, and will be delivered to self-referred participants who are recruited on the basis of experiencing perfectionism as a major concern. Both will be administered via the Internet in order to replicate prior studies of the same mean of delivery. Given that no investigation has previously tested the effects of iUP for perfectionism, no hypothesis regarding, for instance, superiority is possible to provide. However, because iCBT-P was developed specifically for targeting perfectionism, it is assumed to have a greater impact on this particular issue. The clinical trial will involve the following research questions; 1) what are the effects on self-rated perfectionism and psychiatric symptoms of an eight-week Internet-delivered treatment with guidance on demand (iCBT-P)? 2) what are the effects on the same outcomes for iUP? 3) to what extent has treatment affected other domains, such as relationships, as measured using subjective ratings? 4) how are the treatments experienced by the participants themselves, as explored using qualitative interviews?

## Material and methods

2

### Participants and procedure

2.1

Participants will be recruited via advertisements and social media. Those who identify themselves as perfectionists will be referred to a website that has been created specifically for the purpose of the clinical trial. This mean of recruitment has effectively been used before for issues that are not considered to be diagnoses (Rozental et al., 2017), and has the advantage of reaching individuals who themselves regard perfectionism as problematic. The website will consist of general information about the study, the researchers and therapists, ethical issues, and the conditions for their participation. Once an individual signs up to participate, she enters a secure platform using an autogenerated username, e.g., 1234abcd, strong personal password, and six-letter code sent out as a SMS (for more details, see Vlaescu et al., 2016). This type of authorization process is used by many authorities and is regarded to be safe for sharing sensitive data. When the individual is logged on, she then completes a number of questions of demographic nature and all of the self-report measures listed below. These are used to determine eligibility to be included. Those who meet inclusion criteria are later interviewed via telephone using the Mini-International Neuropsychiatric Interview version 7.0 to confirm diagnoses and screen for conditions that are considered a reason for exclusion (MINI; Lecrubier et al., 1997).

Following recruitment, all included participants are randomized by an independent individual not involved in the study. Randomization will be done to the two conditions according to a 1:1 ratio and using a random numbers generator (www.random.org). Treatment content, communication with therapists, technical support, and all self-report measures can be accessible through the secure platform, using the same type of login as described above. Participants will connect their own emails to their autogenerated username, however only notices to log on to the secure platform will be sent out. The treatments are both eight weeks long, after which the participants complete the same type of self-report measures as before (two of them will also be filled out weekly throughout treatment), with a similar procedure being applied at six and 12 months following treatment completion, see Fig. 1 for an overview.

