### Timeline

2.7

The clinical trial is planned to recruit participants in September 2020. The treatments are expected to be completed in November 2020, with the two follow-up assessments being administered in June and November 2021. A submitted manuscript with the final results is planned to be ready in February 2022.

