### Statistical analysis

2.8

In the literature, no prior estimates are available for a power calculation when it comes to what constitutes a reasonable between-group effect size in terms of perfectionism. However, it is reasonable to assume a moderate standardized difference when comparing iCBT-P and iUP on the CPQ in favor of the former. This is based on the assumption that iCBT-P was developed specifically to target perfectionism. Thus, using G*Power to determine the sample size required to detect a Cohen's *d* of 0.50 (α of .05 and β of 0.80) suggest that 64 participants per condition (*n* = 128) will be required for the study. As for the within-group effect size for each condition between screening and post-treatment, the power achieved under these circumstances reveal that it will be possible to detect an effect size *d* of 0.36. The prior study by Zetterberg et al. (2019) demonstrated an effect size *d* of 1.19 on the CPQ for participants receiving iCBT-P with guidance on demand, and > 0.49 for all of the secondary outcomes, which indicates that the current clinical trial should be able to detect a difference on each of the self-report measures.

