In terms of the statistical analyses, differences between conditions and between completers and non-completers will be examined using *t*-tests and Pearson *χ*^2^-tests. Conditional changes over time on both the CPQ and PHQ-9 will be modeled using an intention-to-treat linear mixed-effect model using data from screening, weekly assessment, and post-treatment assessment, and employing random slops, unstructured covariance matrix, and full maximum likelihood estimation with 100 iterations. The other self-report measures have fewer data points and are therefore considered inappropriate for mixed-effects modeling (Hesser, 2015). These will therefore be analyzed using repeated measures analysis of variance and using multiple imputation to deal with missing data. Effect sizes *d* will be calculated to determine the standardized differences in means within and between conditions, and 95% Confidence Intervals will be reported. Clinically significant change, criterion A, will be used to identify the number of participants who have recovered in their perfectionism. As perfectionism is not a diagnosis, recovery will be defined as reaching a statistical criterion of two standard deviations of change from the mean in the direction of a functional distribution on the CPQ, and exceeding measurement error as defined by the reliable change index (Jacobson and Truax, 1991). The latter will also be utilized to determine the number of participants who have experienced non-response and reliable deterioration (Rozental et al., 2014a).

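### Allocation appears to be done in one batch after screening scores and diagnoses are known, but neither the draw nor the between-condition effect sizes are stated to use them: a small, cheaply recovered loss of precision

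*Protocol article*

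**What the plan says.** All places are in the protocol article.

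- **Before allocation** (Participants and procedure). After logging on, a person is to provide baseline data: "she then completes a number of questions of demographic nature and all of the self-report measures listed below". Those who meet the inclusion criteria are then "interviewed via telephone using the Mini-International Neuropsychiatric Interview version 7.0 to confirm diagnoses" and to screen for exclusions.
- **Allocation** (same section). "Following recruitment, all included participants are randomized by an independent individual not involved in the study". The method is: "Randomization will be done to the two conditions according to a 1:1 ratio and using a random numbers generator (www.random.org"). No strata, blocks or minimisation are named.
- **Timing** (Timeline). "The clinical trial is planned to recruit participants in September 2020". One recruitment month followed by allocation of all included participants reads most naturally as a single batch, although the article does not say so outright.
- **Analysis** (Statistical analysis). CPQ and PHQ-9 go into a linear mixed model that uses screening, weekly and post-treatment data. The other measures go into repeated measures analysis of variance with multiple imputation. Effect sizes d are to be calculated "to determine the standardized differences in means within and between conditions". No covariate is named, and no baseline adjustment of d is stated.
- **Sample size** (same section). 64 per condition, 128 in total, as the number "required to detect a Cohen's *d* of 0.50" on the CPQ.

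**The concern.** The usual reasons for not balancing an allocation are that the next assignment may become predictable and that strata stay part-filled during accrual. Neither applies when an independent person allocates a complete, fully characterised cohort at once. The trial could balance the arms on screening CPQ and on diagnosis at almost no cost, and as described it does not.

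Diagnosis deserves attention here. Most diagnoses are admitted (Inclusion and exclusion criteria), and the Introduction and Discussion want to compare how specific the two treatments are to perfectionism and to psychiatric symptoms. The comparator was built for depression and anxiety disorders, so diagnostic mix is a plausible prognostic factor. An outcome's own screening score does not fully account for it.

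At stake is the precision of the between-condition estimates and the comparability of the arms in unadjusted summaries, above all the d values if they are taken from raw post-treatment means.

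**Working it through.** **Inputs.** From Statistical analysis: 64 per arm, d = 0.50, alpha 0.05, power 0.80. The screening-to-post correlation r is not given. I assume 0.62, the CPQ test-retest value in Self-report measures, with a range of 0.3 to 0.7. The prevalence of a current depressive or anxiety diagnosis is not given; I assume 50%. All SDs are set to 1.

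**1. The plan's own figures.** A two-sided two-sample t-test for d = 0.50 needs 63.8, so 64 per arm, with power 0.801. A paired t-test with n = 64 and 80% power detects d = 0.356 (stated 0.36). Both reproduce.

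**2. Chance imbalance under the plain draw.**
- Screening CPQ: SE = sqrt(2/64) = 0.177 SD, 95% range 1.96 × 0.177 = ±0.35 SD. The probability of a gap of at least 0.20 SD is 0.26; of at least 0.25 SD, 0.16.
- A diagnosis at 50% prevalence: SE = sqrt(2 × 0.25/64) = 0.088. The probability of a gap of at least 15 percentage points is 0.09.

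**3. SE and power of the post-treatment arm contrast, by analysis.**
- Raw post score: sqrt(2/64)
- Change from screening: sqrt(2/64) × sqrt(2(1 − r))
- Baseline-adjusted: sqrt(2/64) × sqrt(1 − r²)

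| r | Raw post: SE (power) | Change: SE (power) | Adjusted: SE (power) |
|---|---|---|---|
| 0.3 | 0.177 (0.801) | 0.209 (0.660) | 0.169 (0.837) |
| 0.5 | 0.177 (0.801) | 0.177 (0.801) | 0.153 (0.900) |
| 0.62 | 0.177 (0.801) | 0.154 (0.896) | 0.139 (0.947) |
| 0.7 | 0.177 (0.801) | 0.137 (0.952) | 0.126 (0.976) |

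With screening and post as the only two time points, the group-by-time test in a repeated measures analysis of variance is the test on change. The planned analyses therefore sit nearer the middle column than the first, although the weekly data and follow-ups make this an approximation. Relative to change, adjustment multiplies the variance by (1 − r²)/(2(1 − r)) = (1 + r)/2, which is 0.81 at r = 0.62: a 19% reduction.

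**4. Validity.** In simulation at r = 0.62 with plain randomisation and no treatment effect (8,000 runs), the mean difference was zero and type I error was 0.049 (raw post), 0.055 (change) and 0.051 (adjusted).

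**5. What balancing adds.** Sorting by diagnosis, then by screening CPQ, and randomising two to each arm in consecutive blocks of four cuts the SE of the screening CPQ difference from 0.177 to about 0.07 SD. It is not smaller because one block can straddle the two diagnosis groups. Under this scheme the SE of the contrast without adjustment is about 0.146 SD (raw post) and 0.143 SD (change). With adjustment there is almost nothing left to gain: simulated power was 0.945 under plain allocation and 0.946 with allocation stratified at the screening median. Stratifying at the median without adjusting makes the raw post-score test conservative (type I error 0.025).

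**The case against.** The strongest case against is that nothing here is wrong. A 1:1 draw by an independent person is a sound method. Its chance imbalance is already part of the standard error and of the 80% power at 64 per arm. A condensed article may also leave blocking or strata to a fuller protocol. All of this stands, and it is why the point is only a low-cost improvement.

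Three stronger readings are tempting, and the article does not support them.

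- *That the arm comparisons are all unadjusted.* The CPQ and PHQ-9 mixed model and the repeated measures analysis both include the outcome's own screening score, and recovery also requires reliable change from screening. The description fits only the between-condition d values, if they come from post scores, and factors such as diagnosis.
- *That imbalance adds an error comparable with the planned effect.* At r = 0.62 an imbalance at its 95% limit moves a raw post-score contrast by 0.62 × 0.35 = 0.21 SD (0.10 to 0.24 for r from 0.3 to 0.7). Setting this against d = 0.50 counts it twice, because the standard error already contains it. A change-score contrast moves the other way, by 0.13 SD.
- *That only the allocation can deal with diagnosis.* A diagnosis covariate in the model deals with it as well.

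A per-person coin toss could give arms of 53 to 75 (95% range), but the article does not say that one is used. Even a 53/75 split lowers power only from 0.801 to 0.790.

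**Conclusion.** The point holds as a minor matter of efficiency. Information known before allocation is not stated to be used in the draw, and the between-condition effect sizes are not stated to use it either. The comparison remains valid and unbiased.

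At r = 0.62, baseline adjustment alone brings the SE of the arm contrast to 0.139 SD, from 0.177 SD on raw post scores or 0.154 SD on change. The gain over change is larger when r is lower and smaller when r is higher. Balanced allocation mainly makes the arms look alike and steadies unadjusted summaries.

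The conclusion rests on three assumptions: that allocation is a single batch, which the article implies but does not state; that r lies between 0.3 and 0.7; and, for the diagnosis figures and the 0.07 SD, that prevalence is 50%.

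**What to change.** 1. **Statistical analysis (the part that matters).** State that between-condition estimates and d values come from baseline-adjusted models with any current depressive or anxiety diagnosis (yes/no) as a covariate. For measures analysed at few time points, use analysis of covariance with the outcome's screening score. For CPQ and PHQ-9, keep screening as a response and constrain its mean to be common to both arms, so that it is not on both sides of the model.
2. **Participants and procedure (optional).** After recruitment closes, the independent person sorts participants by that diagnosis indicator and then by screening CPQ, forms consecutive blocks of four, and randomises two to each arm within each block. With 128 participants this makes 32 blocks and fixes the arms at 64/64. Use it only together with item 1, because balancing without matching adjustment makes the unadjusted test conservative.

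Item 1 costs a little analysis work and a rewritten model statement. Item 2 costs a slightly more complex allocation, for almost no further power once item 1 is in place. Neither needs new data.
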